### Sample size

After a thorough review of the literature and using the Ene 2.0 [27] software, we calculated that for a statistical power of 90%, with a significance level of 5%, a sample of 30 patients per group will allow us to detect mean differences of 5.5 points on the EPDS between the experimental group and the control group (alpha = 0.05, beta = 0.10, *N* = 126). To achieve this sample, 600 participants in the third trimester of pregnancy will be screened for eligibility. Of the total, about 280 are expected to have at least one risk factor and will progress to the second phase of the study. Of these, we estimate that a quarter of the women will score 7.5 or higher on the EPDS, which would leave approximately 60 women to be randomized to the two arms of the trial.

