### Data processing

Comparisons of baseline characteristics of the sample will be made with χ2-tests for categorical variables and the Student’s t-test or Mann Whitney U test for quantitative variables, depending on the distribution of the data. Differences in mood symptomatology during treatment will be examined using Wilcoxon signed-rank test for the within-group analyses and the Mann–Whitney U test for the between group analyses. The latter will also be used to analyse variation in EPDS scores between groups. On the other hand, cut-off points for the EPDS will be established and differences in the categorical variables created will be analysed with χ2-tests. Linear regression models will be performed for each group to evaluate the influence of the child’s temperament and global and daily activity during treatment on mood symptoms.

Univariate analyses of covariance will be conducted to investigate differences between groups. For this, the independent variable will be the group assignment (treatment as usual plus psychoeducation treatment versus treatment as usual alone) and the dependent variables will be the respective clinical or functional outcome scores post-treatment. This analysis will be performed on an intention-to-treat basis, with women being analysed in the treatment group to which they were randomized. In addition, a logistic regression model will be used to assess the relationships between clinical variables.

Finally, we will also build an ordinal regression model to explore factors associated with having depression after the intervention. The categorical variable of the EPDS assessed post-intervention will be used as the dependent variable, while risk factors evaluated at baseline will be the independent variables.

The outcomes will be reported with 95% confidence intervals. All data will be analysed using IBM SPSS Statistics v22.

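### The analysis of covariance names no covariate and no EPDS comparison is named as deciding; make a baseline-adjusted ANCOVA of post-intervention EPDS the primary analysis

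*Protocol article*

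**What the plan says.** All the between-group analyses are in the Data processing section of the protocol article.

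- **Rank tests.** Mood symptomatology during treatment is to be examined with the "Wilcoxon signed-rank test for the within-group analyses and the Mann–Whitney U test for the between group analyses". Of the Mann-Whitney test the text adds: "The latter will also be used to analyse variation in EPDS scores between groups".
- **Categories.** "cut-off points for the EPDS will be established and differences in the categorical variables created will be analysed with χ2-tests".
- **Covariance analysis.** "Univariate analyses of covariance will be conducted to investigate differences between groups". The model is then defined: "the independent variable will be the group assignment (treatment as usual plus psychoeducation treatment versus treatment as usual alone". Its outcomes are the clinical and functional scores after treatment. No covariate follows. Intention to treat is stated for this analysis and for no other.
- **Reporting.** "The outcomes will be reported with 95% confidence intervals".

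The Sample size section sizes the trial to "detect mean differences of 5.5 points on the EPDS" with 30 women per group. The EPDS is the only mood instrument (Mood assessment). Every woman who is randomised has an EPDS from day 8 to 15 after delivery, because that score decides her eligibility. Both groups are assessed at baseline and at 6 weeks (end of the Exclusion criteria section). No section names or ranks a primary analysis.

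**The concern.** A covariance analysis with one two-level factor and no covariate is a one-way analysis of variance, which is the two-sample t-test on post scores. The method's name and its definition therefore disagree, and the obvious covariate, already measured in every randomised woman, is left out of the between-group model.

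The same outcome is also tested between groups by rank tests and by chi-square, and nothing says which result answers the trial's question. With about 60 women these tests can disagree. If the choice among them can be made after the data are seen, the nominal 5% error rate no longer holds. The estimand is unclear too: the sample size rests on a mean difference, which a Mann-Whitney test does not estimate.

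**Working it through.** **1. The plan's own figure.** For two means, n per group = 2(1.960 + 1.282)² SD² / 5.5². The article gives no SD, so 30 per group cannot be reproduced, only inverted: SD = 5.5 / (3.242 × √(2/30)) = 6.57. The calculation is one for a difference in means, so it fits a t-test or ANCOVA and not a rank test.

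**2. The between-group EPDS comparisons, side by side.**

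| Comparison | Scale | Uses baseline EPDS? | Stated as intention to treat? |
|---|---|---|---|
| Mann-Whitney, mood during treatment | ranks | not stated | no |
| Mann-Whitney, variation in EPDS | ranks | yes, if variation means change | no |
| Chi-square, cut-offs to be set | proportions | not stated | no |
| Covariance analysis of post scores | means | no covariate listed | yes |

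**3. False-positive rate if any of three may decide.** The three are a t-type test on post scores, Mann-Whitney on post scores and Mann-Whitney on change. Assumptions, none of them in the article: EPDS Normal with mean 5 and SD 3.7, rounded to whole points; test-retest correlation 0.3, 0.5 or 0.7 before selection; baseline at least 8 (the first whole score above 7.5), with and without an upper limit of 12; 30 per arm; no effect.

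- With selection, 3,000 null trials per setting: at least one p < 0.05 in 7.3-8.2%. Repeat runs of the same set-up ranged from 6.4% to 9.3%, so about 7-9% is a fair summary.
- Without selection (standard normal data, correlation 0.2-0.7, 6,000 trials per setting): 8.9-10.1%.
- Adding chi-square tests: 10.5-13.1% with selection (cut-offs 8 and 13), and 11.3-12.3% without selection (one cut at the median).

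Three independent tests would give 1 − 0.95³ = 14.3%. The simulated rates are lower because the tests are correlated.

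**4. What baseline adjustment gains.** The share of post-score variance removed is r², where r is the correlation within the randomised sample. Selection on baseline narrows its range, so r falls to 0.11-0.43:

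- 0.11² = 0.01 and 0.43² = 0.18, that is, 1-18% of post-score variance.
- Against a change-score comparison the variance ratio is 1.02-1.14, a saving of 1 − 1/1.02 = 2% to 1 − 1/1.14 = 12%.

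On the power scale, with the implied SD of 6.57 and 30 per arm, power for 5.5 points rises from 90.0% to 91.1% at r = 0.2 and to 92.5% at r = 0.3.

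**5. Chance imbalance.** Suppose one arm starts Δ points higher and the slope of post score on baseline is β. With no treatment effect, the post-score difference shifts by βΔ and the change-score difference by (β − 1)Δ. With equal SDs β equals the correlation before selection. For Δ = 1 and β from 0.3 to 0.7, the shifts are +0.3 to +0.7 and −0.7 to −0.3 points, in opposite directions. ANCOVA with baseline as covariate removes both.

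**The case against.** The article does not say that group is the only predictor. The name of the method implies covariates, and a condensed article may leave the list to the full protocol or analysis plan. The covariance analysis also looks like the intended main one: it is introduced for group differences, it alone is stated to be intention to treat, and it can give the mean difference and confidence interval that the sample size and reporting statements call for. Planning a rank test beside an analysis of means is common.

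Part of this stands: the text leans towards the covariance analysis. But the article does set out the model, giving its independent and dependent variables, and does so incompletely beside competing tests that it does not rank. That is a badly fixed analysis, not merely a missing detail.

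Three stronger readings are tempting and are not supported.

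- A reader might infer that baseline EPDS is never used. The within-group Wilcoxon test uses it, and so does any test of change; it is absent only from the between-group model as defined.
- A reader might infer that the unadjusted comparisons are biased. Under 1:1 randomisation they are unbiased over repeated randomisation; the shifts in the working are conditional on a chance imbalance.
- A reader might infer that separate rank tests of post score and of change are explicitly planned. That is an interpretation: variation probably means change, and mood during treatment could mean the post score, the change or the interim assessments.

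**Conclusion.** The point holds. As written, the covariance analysis is an unadjusted comparison of post scores, several other comparisons of the same EPDS outcome stand beside it, and none is named as deciding. If the t-type test or either rank test could decide, the error rate at 30 per arm is about 7-9% instead of 5% with selection on baseline, about 9-10% without it, and higher with chi-square tests. These rates rest on an assumed SD, an assumed correlation and the reading of the two rank tests given above.

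The precision gain is modest and uncertain, roughly 1-18% of post-score variance for a test-retest correlation of 0.3-0.7 before selection. The stronger reasons to act are that the deciding test becomes fixed and that the result no longer depends on chance baseline imbalance.

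**What to change.** State in the Data processing section that the primary analysis is a linear model (ANCOVA) of EPDS at the 6-week post-intervention assessment on randomised arm, with baseline EPDS (day 8 to 15) as covariate. Analyse all women in the arm to which they were randomised, and report the adjusted mean difference with its 95% CI. Label the Mann-Whitney, change-score and chi-square comparisons as supportive, and say for each whether it uses the post score or the change from baseline.

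The cost is wording only. The baseline EPDS is already collected from every randomised woman, and no visit, measurement or sample size has to change. The change should be made before outcome data are analysed; the Trial status section describes recruitment as still open.

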Psychological therapy for depression has shown to be an effective treatment in depressed patients of all ages and all degrees of severity, including PPD [20]. Given the consequences of the disease, another strategy would be to administer preventive treatment with a lasting effect that could protect women against developing this type of depression. A systematic review found that 13/17 studies with successful psychological treatment targeted an at-risk population, and 4/7 trials using interpersonal therapy demonstrated success of the intervention versus a control condition [8].

The aim of this study was to identify women at risk of PPD using a protocol [21], investigate the efficacy of a structured programme of psychoeducational therapy designed ad hoc in preventing the development of PPD in at-risk women and explore prognostic factors for this type of depression.

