## Methods/Design

We registered this single-blind randomized clinical trial in 2014 (identifier NCT02323152). Women will be recruited in the third trimester of pregnancy from 2015 to the completion of the study. Women that agree to participate and sign the informed consent form will then be assessed through a first screening visit by their reference midwife; specifically, the midwife will record sociodemographic data and the presence of various previously described risk factors, including the personality vulnerability of the woman and her socioeconomic status.

Women with at least one risk factor will progress to the next phase of the study and will be assessed between 8 and 15 days after the birth of their baby, at the Araba University Hospital. Clinical data will be collected relating to the delivery. We will also evaluate the women’s mood with the Edinburgh Postnatal Depression Scale (EPDS) [22], the child’s temperament with the Merrill-Palmer-Revised Scales of Development [23] and the current and overall physical activity of women with the International Physical Activity Questionnaire (IPAQ) [24] and Global Physical Activity Questionnaire (GPAQ) [25] using the Spanish versions of these tools. A score between 7.5 and 12.5 on the EPDS indicates depression risk and women with scores in this range will progress to the next phase of the study. In this phase, the participants will be randomized with Random Allocation Software 1:1 to the experimental or control group (treatment as usual). Women in the experimental group will receive six (1 individual and 5 group) sessions of the psychoeducational intervention and their status will be evaluated weekly. The control group will continue to have regular appointments with the midwife and gynaecologist and will be assessed again 6 weeks after inclusion in the trial.

We will recruit patients from five health centres in Vitoria and two health centres in Donostia, and the study is being coordinated by the Psychiatry Research team of Araba University Hospital, which is a member of the Center for Biomedical Research Mental Health Network (CIBERSAM). Patients meeting all the inclusion criteria and none of the exclusion criteria (listed below) will be included in the study.

The trial will be conducted in accordance with good clinical research practice, enabling the research to be carried out with low risk of bias and a high degree of external validity.

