### Mood assessment

The **EPDS** will be used to assess participants’ depressive symptoms [22]. This 10-item self-report tool is designed to screen women for symptoms of emotional distress during pregnancy and the postnatal period.

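### The exploratory model of baseline risk factors uses only a categorised post-intervention EPDS, which costs some power in about 60 women; the full score should be modelled first, with the categories as support

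*Protocol article*

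**What the plan says.** All references are to the protocol article.

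- **Aim.** The last paragraph of Background includes, beside efficacy, the aim to "explore prognostic factors for this type of depression".
- **Model for that aim.** In Data processing, "we will also build an ordinal regression model to explore factors associated with having depression after the intervention". Its outcome is then fixed: "The categorical variable of the EPDS assessed post-intervention will be used as the dependent variable, while risk factors evaluated at baseline will be the independent" […].
- **Categories.** Their number and limits are open. Earlier in the same section, "cut-off points for the EPDS will be established and differences in the categorical variables created will be analysed with χ2-tests". I take the ordinal model to use categories formed in this way, since no others are described.
- **Instrument.** Under Mood assessment the EPDS is described thus: "This 10-item self-report tool is designed to screen women for symptoms of emotional distress during pregnancy and the postnatal period".
- **Score analyses elsewhere in Data processing.** EPDS scores are compared between arms by the Mann–Whitney test. In the analysis of covariance "the dependent variables will be the respective clinical or functional outcome scores post-treatment". Linear regressions on mood symptoms cover child temperament and physical activity.
- **Number of women.** Sample size describes a screening funnel "which would leave approximately 60 women to be randomized to the two arms of the trial".

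**The concern.** The treatment comparison has score-based analyses beside its categorical one. The model for the listed baseline risk factors has none: the linear regressions are confined to temperament and activity, and the analysis of covariance names only group assignment as independent variable. The logistic model is described too loosely to fill the gap.

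Banding treats all women within a band as alike, and it counts a one-point difference across a limit as a whole category. In a small sample this makes a real factor easier to miss and its interval wider, and the answer depends partly on where the limits fall. Six risk factors are listed and about 60 women are expected, so there is little information to spare. The Abstract says the findings will feed the design of a definitive study, so a factor missed here may have consequences there.

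**Working it through.** **Inputs from the document.** About 60 women, 30 per arm, two-group difference 5.5 EPDS points, 90% power, 5% significance (Sample size). EPDS values 7.5 and 12.5 (Methods/Design: "A score between 7.5 and 12.5 on the EPDS indicates depression risk").

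**Not in the document, so assumed.** SD of the score, number and limits of the categories, effect and prevalence of a risk factor, and the score range (0 to 30 in the simulations). The tests are two-sided.

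**Step 1: what SD does the plan's own figure imply?** No SD is given, so 30 per arm cannot be reproduced, only inverted:

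- d = (1.960 + 1.282) × √(2/30) = 3.242 × 0.2582 = 0.837
- SD = 5.5 / 0.837 = 6.57

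The same sentence also prints N = 126. With 63 per arm, d = 3.242 × √(2/63) = 0.578 and SD = 5.5 / 0.578 = 9.52. No single SD fits both totals. I use about 60, the number the funnel text expects to randomise, and SDs from 4 to about 6.6.

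**Step 2: three bands cut at 7.5 and 12.5.** n = 60, one binary factor, integer scores, 2,000 replicates per row. The effect is set for about 80% power on the score:

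- prevalence 50%: d = (1.960 + 0.842) × √(1/30 + 1/30) = 0.723
- prevalence 30%: d = 2.802 × √(1/18 + 1/42) = 0.789

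The comparison is linear regression on the score against a proportional-odds likelihood-ratio test on the bands. Losses were taken before rounding.

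| SD | Mean | 50%: score / bands | Loss, points | 30%: score / bands | Loss, points |
|---|---|---|---|---|---|
| 4 | 7 | 76.7% / 65.4% | 11.3 | 79.2% / 67.8% | 11.4 |
| 4 | 9 | 78.8% / 72.0% | 6.8 | 77.3% / 70.0% | 7.3 |
| 5 | 7 | 77.3% / 65.2% | 12.1 | 78.3% / 68.2% | 10.1 |
| 5 | 9 | 77.6% / 70.2% | 7.5 | 78.6% / 69.9% | 8.7 |
| 6.57 | 7 | 79.6% / 69.2% | 10.4 | 77.0% / 67.9% | 9.0 |
| 6.57 | 9 | 78.0% / 69.6% | 8.4 | 79.6% / 70.1% | 9.5 |

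The loss is about 7 to 12 points.

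**Step 3: a second simulation with other effects and a rank test.** 3,000 replicates, SD 4 to 6.5, differences of 2.5 to 5.5 points, reference means 7 to 10, same bands. The full score gained about 5 to 13 points throughout. In one example (prevalence 50%, SD 6.5, difference 5.5, reference mean 8), power was 89.6% for linear regression, 88.0% for a rank test of the full score (the score test of a cumulative-logit model) and 81.0% for the bands. The loss is 89.6 − 81.0 = 8.6 points against the first and 88.0 − 81.0 = 7.0 against the second. The gain therefore does not depend on assuming normality.

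**Step 4: sensitivity to the categories.** n = 60, d from 0.3 to 1.0, prevalence 50% or 30%, limits at quantiles, 800 replicates:

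- three categories: losses of 3.2 to 12.5 points
- four equal categories: losses of 1.9 to 5.4 points

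For a continuous factor with about 80% power on the score, three categories lost 8.8 or 15.5 points, depending on the limits.

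**The case against.** **The stated target is depression, not a mean score.** The model is meant to find factors associated with having depression afterwards, and a model of EPDS points answers a neighbouring question. This stands in part. It is a reason to keep the ordinal model, and a reader should not infer that the model is wrong or should go. But no diagnostic interview is named for this outcome. Depression is represented here by bands of the EPDS, which contain nothing that the score does not.

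**Ordinal regression keeps the order of the categories.** True, and the loss is smaller than with a two-way split. The simulations already compare against ordinal methods, and a loss remains.

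**The size is not a figure for the planned model.** This stands. The bands, SD and effect are assumed, and one factor at a time was tested, whereas the plan would enter several. Nothing in the document supports a 5.5-point difference for a risk factor; that is the treatment difference used for sizing.

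**Prognostic work is not confined to the ordinal model.** Correct. Child temperament, which Background lists as a risk factor, is studied by linear regression, as is activity. The point is limited to the baseline risk factors listed in the inclusion criteria.

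**The model is exploratory and comes last.** Also correct, and it limits the consequence. It does not make the loss of information useful.

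**Conclusion.** The point holds as a cheap improvement to an exploratory analysis that serves a stated aim. For the listed baseline risk factors only the categorised EPDS is modelled, and in about 60 women this gives up power. The loss is roughly 5 to 13 percentage points given three bands at 7.5 and 12.5, one binary factor and an SD of 4 to 6.5, and about 2 to 5 points with four equal categories. It could be larger for a continuous factor.

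The documents do not support two stronger readings:

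- **That the efficacy analysis is weakened by the χ²-test on EPDS categories.** It is not. EPDS scores are also compared between arms by Mann–Whitney, and post-treatment scores by analysis of covariance, so the χ²-test is an addition.
- **That 5 to 13 points is a property of the plan.** It is conditional on the assumptions above. The open cut-offs are not counted as a fault, since an analysis plan may fix them.

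**What to change.** In Data processing, make the full post-intervention EPDS score the dependent variable of the main prognostic analysis, with the baseline risk factors as independent variables. Use linear regression or, if the score is skewed, a cumulative-logit model on the uncollapsed score. Keep the ordinal regression on EPDS categories and label it supportive, for the clinical question of having depression.

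The cost is a change of wording; no further data, visits or participants are needed. The main prognostic result would be in EPDS points (or a cumulative odds ratio) and not in depression categories, and the retained ordinal model covers that need.

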## Discussion

This study will provide information about the effectiveness of a new psychoeducational programme specifically designed to prevent PPD in at-risk women. Should it be found to be effective, this programme could have an important role in preventing this type of depression, a severe mental illness, and its deleterious consequences both in women and in their family including the newborn infant.

The strengths of the study include targeting a defined sample of pregnant women at risk of depressive disorder according to the literature reviewed. The implementation of a preventive programme focused on the mental health of women during pregnancy and the postpartum period is, in itself, an important aspect of the study, as existing postpartum care programmes tend to be related to the baby and the reproductive system of the woman, as well as the treatment of health problems, but not to prevention. With this study, we underline that it is essential to pay close attention to the overall wellbeing of women including their mental health, especially in women with recognized risk factors.

